#### Secondary outcomes

The secondary outcomes include: (1) the frequency of angina attacks from baseline to 4 weeks after the acupuncture treatment, (2) the pain intensity of angina which is assessed by visual analog scale (VAS), (3) total ischemia burden (TIB) and heart rate variability (HRV) which are recorded by 24-h dynamic electrocardiogram (DCG), (4) QT dispersion (QTd) which is recorded by ECG, (5) the score of Seattle Angina Questionnaire (SAQ), (6) the score of Short-Form of McGill Pain Questionnaire (SF-MPQ), (7) the score of self-rating anxiety scale (SAS), (8) the score of self-rating depression scale (SDS), and (9) the expectation values of acupuncture treatment which is composed of 7 questions and designed by our team. The VAS score will be extracted from the angina diaries. The second to eighth secondary outcomes will be evaluated at baseline, at the end of acupuncture treatment and at the end of follow-up. Moreover, the expectation of acupuncture treatment in each patient will be evaluated at baseline.

### Patient safety

To guarantee the safety of patients, acupuncture treatment will be performed in the cardiology department where cardiovascular specialists and first-line physicians can participate in emergency timely. All adverse events (AEs) such as pain, allergy, bleeding, hematoma, and fainting should be recorded in the case report form (CRF) carefully. Serious adverse events (SAE) such as death or life-threatening events should immediately be reported to the principal investigator.

### Practitioners training and quality control

All researchers involved in this trial must attend training classes to ensure all practices at each center are generalized and standardized according to the standard operating procedures (SOP). All the acupuncture manipulation will be performed by two licensed acupuncturists with clinical experience over 3 years. The acupuncturists should pass the examination on the SOP of acupuncture intervention before participating in this trial. In addition to the monthly inspection carried out by the research team, a specialized project supervision team will be established by the Clinical Research Center for Acupuncture and Moxibustion of Sichuan Province, and responsible for monitoring the study every 3 months.

### Data management

Data will be managed jointly by the two research centers. All the data will be recorded with printed and electronic case report forms CRFs. Only outcome assessors have access to CRFs and will perform the double-data entry.

### Data analysis

All analyses will be strictly conducted according to the intention-to-treat (ITT) principle. Continuous variables will be described with means and standard deviation (SD) or median, maximum, minimum, P25, and P75. Categorical variables will be described with numbers and percentages (%).

For the frequency of angina attacks from baseline to 4 weeks after inclusion, if the distribution conforms to the approximately normal distribution, analysis of covariance (ANCOVA) will be used. Since this study is a multicenter clinical trial, the center effects will be included in the analysis model. Age, gender, duration of the disease, and study site will be included in the model as covariates. Considering clustering effects of the number of angina attacks per patient, a hierarchical Poisson regression will be conducted exploratively. Separate ANCOVA analyses will be performed for secondary outcomes. The incidence of AEs in both groups will be compared with a Poisson regression model in which the number of participants with AEs is an independent variable and the group is a dependent variable.

Missing data will be imputed by multiple imputation. A sensitivity analysis using a pattern-mixture model will be conducted to assess the robustness of the results.

For all statistical analyses, Statistical Analysis System version 9.4 software (SAS Institute Inc., Cary, North Carolina) will be used. A *P* value of less than 0.05 (*α* value of 0.05, two-sides) will be considered statistically significant.

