## Methods and design

### Study design

This is a two-arm, double-center, randomized controlled trial. A total of 148 CSAP patients will be enrolled and randomly assigned to two groups through central randomization in a 1:1 ratio. This trial will include a 2-week screening period, a 4-week treatment period, and a 4-week follow-up period. Outcome assessments will be performed at the baseline, the end of treatment, and the end of follow-up (see Fig. 1 for the details of the study schedule).

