### Sample size

In this study, we assume that H0 represents the clinical effect of Group A is the same as Group B; H1 represents the effect of Group A is not the same as Group B.

According to the formula: $$ n=\frac{2{\sigma}^2}{{\left(\mu 1-\mu 2\right)}^2}\times {\left({\mu}_{\alpha /2}+{\mu}_{\beta}\right)}^2 $$ [23]. In this study, assuming α = 0.05 (both sides), 1-β = 0.80. Based on our previous study [12], *μ*1 is the improvement of the frequency of angina attacks in the acupoints on the disease-affected meridian group, and *μ*2 is the improvement of the frequency of angina attacks in the acupoints on the non-affected meridian group. With *μ*1 = 5.57 and *μ*2 = 3.14, σ is estimated to be 5, and the sample size is calculated as 67 per group. Considering a dropout rate of 10%, we concluded that the sample size is 73.6 per group, and each group needs 74 cases after taking an integer. Therefore, a total of 148 CSAP patients will be finally recruited.

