### Intervention

All patients in the two groups will receive a total of 7–9 acupuncture sessions (at least 7 sessions) during 4 weeks. By intradermal needle, acupuncture stimulation will last for 48–72 h in each session with a 1-day interval between each session.

The acupoint prescription will be composed of the basic acupoints and additional acupoints. The basic acupoints include bilateral *Xinshu* (BL15) and *Juque* (CV14), which are close to the heart. The basic acupoints will be used for the patients in both groups. The additional acupoints are all on the forearm, which are far from the heart relatively. For group A, 3 additional acupoints on the Heart Meridian will be selected, including bilateral *Shenmen* (HT7), *Yinxi* (HT6), and *Tongli* (HT5). For group B, 3 additional acupoints on the Lung Meridian will be selected, including bilateral *Taiyuan* (LU9), *Lieque* (LU7), and *Kongzui* (LU6) (Fig. 3).

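### The strict ITT rule, as written, also covers the adverse-event comparison; a set of needled patients, grouped by prescription received, suits it better (minor)

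*Protocol article*

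**What the plan says.** The Data analysis section of the protocol article opens with one rule for the whole plan: "All analyses will be strictly conducted according to the intention-to-treat (ITT) principle". Later in the same section comes the safety comparison: "The incidence of AEs in both groups will be compared with a Poisson regression model". No separate population is named for it, and no part of the article mentions a safety set, grouping by treatment received, or an exception to ITT for AEs.

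The Patient safety section describes what is collected: "All adverse events (AEs) such as pain, allergy, bleeding, hematoma, and fainting should be recorded in the case report form (CRF) carefully". It adds serious events such as death or life-threatening events. The Intervention section says of the two points near the heart: "The basic acupoints will be used for the patients in both groups". The arms therefore differ only in the three forearm points.

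**The concern.** Several of the listed AEs (allergy, bleeding, hematoma, needle pain) are mainly reactions to an inserted needle or its tape. A patient who is randomised but never needled cannot have a needle reaction, yet under the stated rule still counts in the denominator. A patient who receives the other arm's forearm points has any reaction counted against a prescription that was not applied.

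Including untreated patients is the cautious choice for an efficacy contrast, but for needle-related AE incidence it lowers the figure. The absolute incidence matters here as well as the contrast. The Background and the section on acupuncture modality selection justify the intradermal needle partly by its safety and fewer adverse reactions, and the Discussion expects the results to guide the choice of modality.

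**Working it through.** **Inputs from the protocol article.** Study design: "A total of 148 CSAP patients will be enrolled and randomly assigned to two groups through central randomization in a 1:1 ratio", which is 74 per arm. Sample size: "assuming α = 0.05 (both sides), 1-β = 0.80", mean improvements 5.57 and 3.14, SD 5, dropout 10%.

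**The plan's own figure.** n = 2 × 5² × (1.960 + 0.842)² / (5.57 − 3.14)² = 66.46, rounded up to 67, as stated. Then 67 × 1.10 = 73.7, rounded up to the stated 74. The 74 serves below only as the denominator.

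**Inputs the document does not give (assumptions).** The number never needled per arm, k, is taken as 2 to 7. The top value is about the whole dropout allowance (10% of 74 = 7.4), so it supposes that nearly all dropout happens before the first needle. The incidence in needled patients, r, is taken as 20% for illustration. The share needled at the other arm's points, c, is taken as 1% to 5%.

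**Dilution in one arm.** With AE incidence b in unneedled patients, the incidence over all randomised patients is [(74 − k) × r + k × b] / 74. Setting b = 0 gives the greatest dilution:

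| k | (74 − k)/74 | r = 20% reads as |
|---|---|---|
| 0 | 1.000 | 20.0% |
| 2 | 0.973 | 19.5% |
| 4 | 0.946 | 18.9% |
| 7 | 0.905 | 18.1% |

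At k = 7 the expected number of patients with an AE is 0.20 × 67 = 13.4, against 0.20 × 74 = 14.8 had all been needled: 1.4 fewer. Any b above 0 brings the figure back towards 20%.

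**Ratio between arms.** Again with b = 0:
- If k is the same in both arms, the factor cancels and the ratio is unchanged.
- If 10% of one arm and none of the other is never needled, a true ratio of 2.00 becomes 2.00 × 0.90 = 1.80 or 2.00 / 0.90 = 2.22.
- If all 7 fall in one arm and there is no true difference, the ratio is 67/74 = 0.91.

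**Wrong-arm needling.** Take true incidences of 20% and 10%, with a share c of each arm needled at the other arm's points. The ratio is [(1 − c) × 0.20 + c × 0.10] / [(1 − c) × 0.10 + c × 0.20]. At c = 1% it is 0.199/0.101 = 1.97; at c = 5% it is 0.195/0.105 = 1.86. The twofold difference is itself generous for arms that share BL15, CV14 and the needle type. With equal incidences c has no effect.

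**Against sampling error.** The standard error of a 20% incidence in 74 patients is √(0.20 × 0.80 / 74) = 4.6 percentage points. The largest shift in the table is 1.9 points.

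**The case against.** The strongest objection is that the opening sentence is a general declaration in a condensed article, and that analysis sets are normally defined in the full protocol or SAP, which are not shown. A missing safety set would indeed be no finding. Here, however, the article fixes a rule for every analysis and calls it strict, so a later document would have to depart from that sentence to use a safety set. The point survives as one about stated text.

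Other parts of the objection stand:
- Comparing AEs by assigned arm is a valid randomised comparison, of assignment and not of exposure. It is not a miscalculation, and grouping by treatment received gives up some of that protection.
- The AE definition covers all events. Pain, allergy and fainting can occur without a needle, so dilution of all-AE incidence is smaller than the table shows.
- Needling is done by two licensed acupuncturists examined on the operating procedures, which makes wrong-arm needling unlikely to be common.

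Two stronger readings are tempting, but the document does not support them. A reader might infer that AE incidence will be distorted and that risk will always be understated. If no patient goes unneedled or is wrongly needled, the distortion is zero, and wrong-arm needling can raise an arm's incidence as well as lower it. A reader might also infer from the general multiple-imputation sentence that unneedled patients will be given imputed needle reactions. Nothing says that AEs will be imputed. They are recorded in the case report form as events, and a patient with none recorded does not thereby have a missing value.

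**Conclusion.** The point holds as a minor mismatch between a stated rule and the question the AE comparison should answer. If some randomised patients are never needled, needle-related AE incidence in that arm is diluted by their share. Under the assumed counts that is at most about 2 percentage points on a 20% incidence, well inside sampling error. The between-arm ratio changes only if the share differs by arm, and the effect of wrong-arm needling is limited. All of this rests on assumed counts and an assumed AE rate, since the document gives neither. The wording is worth changing because the correction is cheap and customary, not because the trial's conclusions are at risk.

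**What to change.** In the Data analysis section, limit the ITT sentence to the primary and secondary efficacy outcomes. Add that AEs are summarised and compared in all patients with at least one intradermal needle inserted, grouped by the prescription received, using observed AEs only. The comparison by assigned group can be kept as a supportive analysis. Make the change before unblinding, so that the AE population is not chosen with results in view.

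The cost is a sentence or two and one extra population flag. No new data are needed, provided the treatment record shows whether a needle was inserted and at which points. The downside is that the main AE comparison is no longer strictly by randomised group, which the supportive analysis covers.

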### Inclusion criteria

The patients will be included if they meet the following 6 items: (1) match the diagnostic criteria of SCAD; (2) meet the criteria of Class I or Class II according to the Canadian Cardiovascular Society (CCS) angina pectoris severity grade [22]; (3) age from 45 to 70 years; (4) have experienced angina attack in the last 3 months, and the attack frequency ≥ twice a week in the most recent month; (5) have a standardized medication history at least 2 months before enrolment (sustaining the same medication, usage, and dose), the basic therapeutic medication retains to one or more of the following: β-blockers ACEI, ARB, and antiplatelet medications and statins; and (6) have signed the informed consent.

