### Outcomes

#### Primary outcome

In this trial, the primary outcome is the frequency of angina attacks from baseline to 4 weeks after inclusion. The frequency of angina attacks will be recorded in the angina diary. The angina diary will be requested to complete and return to assessors in time by paper diary, emails, short messages, or telephone calls throughout the whole 10 weeks observation period.

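### The primary ANCOVA applies only if the attack frequency looks normal, with no criterion and no confirmatory analysis otherwise; the condition is unnecessary and should be deleted

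*Protocol article*

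**What the plan says.** The Primary outcome section states that "the primary outcome is the frequency of angina attacks from baseline to 4 weeks after inclusion", recorded in an angina diary kept throughout the 10 weeks of observation.

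The Data analysis section then gives the analysis of that outcome as a conditional: "if the distribution conforms to the approximately normal distribution, analysis of covariance (ANCOVA) will be used". Age, gender, disease duration and study site are the listed covariates; baseline attack frequency is not among them. The section does not say what happens if the condition is not met. The only other model for this outcome is introduced because of clustering of attacks within patients: "a hierarchical Poisson regression will be conducted exploratively". The pattern-mixture analysis mentioned there concerns missing data. For the other endpoints there is no condition: "Separate ANCOVA analyses will be performed for secondary outcomes".

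The Sample size section rests on a comparison of mean improvements: "With *μ*1 = 5.57 and *μ*2 = 3.14", and "σ is estimated to be 5, and the sample size is calculated as 67 per group". The Blinding section says that statisticians will not know the group allocations.

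**The concern.** A confirmatory analysis should be identifiable before the outcome data exist. Here it is identifiable only if the data pass a check that is not described. The text does not say whether the check is formal or visual, or whether it is applied to the 4-week count, the change from baseline or the model residuals. If the check fails, the article offers no primary test.

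That branch is not remote. The outcome is a count that cannot fall below zero, and eligibility requires "the attack frequency ≥ twice a week in the most recent month", which cuts off the lower end at entry. A long right tail is plausible.

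Four things are at stake: whether the primary test is defined at all; power, if the substitute is less efficient than ANCOVA; agreement between the analysis and the comparison of means that sized the trial; and the 5% level, should someone choose among candidate tests by their results.

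**Working it through.** **1. The plan's own figure.** Inputs from the Sample size section: "assuming α = 0.05 (both sides), 1-β = 0.80", means 5.57 and 3.14 (difference 2.43), SD 5.

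n per group = 2σ²(z₀.₉₇₅ + z₀.₈₀)² / (μ1 − μ2)² = 2 × 25 × (1.960 + 0.842)² / 2.43² = 66.46, rounded up to 67.

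This reproduces the stated 67; with 67 analysed per group, power is 80.3%. Adding 10% gives 67 × 1.10 = 73.7, hence 74 per group and 148 in total. The calculation is for a difference in means, so it supports the ANCOVA branch and no other.

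**2. Assumptions for the simulations.** The article gives no distribution for the counts, so everything below is assumed. All scenarios use 67 per group.

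- *Set A:* weekly attack rate 2 + Gamma(1,1); baseline is a 2-week Poisson count doubled to a 4-week scale; outcome is a 4-week Poisson count with mean response 0.65 and lognormal spread 0.2, 0.4 or 0.6.
- *Set B:* gamma-Poisson counts with baseline at least 8 per 4 weeks (2 per week × 4), three parameter choices, 2,000 null trials each. The simulated SD of change was 5.8 to 8.2 against the planned 5, so this set is illustrative.

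**3. Would the condition be met?** The check used here is Shapiro-Wilk at 5%; the article names none.

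| Quantity judged | Share of null trials rejecting normality |
|---|---|
| 4-week count | about 100% (A and B) |
| ANCOVA residuals | 88–100% (A); over 99% (B) |
| Change from baseline | roughly 40–70% (A) |

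The same data can pass or fail depending on a choice that the article leaves open.

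**4. Is the condition needed?** Type I error of a baseline-adjusted ANCOVA used whatever the distribution: 4.4–5.5% (A) and 4.5–4.9% (B). It is not needed to protect the 5% level.

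**5. What happens under different ways of switching?**

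| Rule | Two-sided type I error |
|---|---|
| Normality check, then ANCOVA or a rank test (A) | 4.9–5.8% |
| Better p-value of ANCOVA and rank test (B) | 6.8–7.8% |
| Same, with log-scale ANCOVA added (B) | 8.0–9.4% |
| Smallest p-value of ANCOVA, rank test on change, rank test on count, quasi-Poisson (A) | about 11–12% |

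Only the last three rows select on the treatment result.

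**6. Power.** In set A, sending the analysis to a rank test on change when normality fails lowered power from about 70% to 37%, 52% to 26% and 35% to 21% for the three response spreads. A rerun with an assumed 20% lower attack rate in one group gave powers of this order. That effect is 0.20 × (4 weeks × 3 per week × 0.65) = 0.20 × 7.8 = 1.56 attacks, smaller than the planned 2.43, so these are not estimates of the trial's power. Much of the loss comes from subtracting a noisy 2-week baseline scaled up to 4 weeks, which regression on baseline avoids.

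**The case against.** **The article condenses a fuller protocol.** An analysis plan that is not shown may name the check and the fallback. That is fair, and it rules out saying that the trial has no fallback anywhere. But the article chose to state the decision rule and stated half of it. The condition is itself the poor choice, since an unconditional analysis is available and works.

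**The condition may well pass.** The article asks only for approximate normality, which is looser than a formal test, and the sample size is framed on improvement. If change is what is judged, it passes in a good share of simulated trials. This stands: the undefined branch is plausible, not certain.

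**A reader might infer that the 5% level is lost.** The documents do not support that. The condition concerns the distribution, not the treatment effect, and a switch of that kind held error near 5%. Statisticians are to be blind to allocation, which makes selection by result harder, although p-values for coded groups could still be seen. The 11–12% is a worst case under deliberate choice of the smallest p-value, which the article does not describe.

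**A reader might also take SD 5 against mean improvements of 3.14 and 5.57 as proof of skewness.** It is not. An improvement can be negative, so its SD may exceed its mean without any skew. The case for skewness rests on the outcome being a bounded count in patients selected at entry.

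**Conclusion.** The point holds in a limited form. As written, the primary test is conditional on an unspecified check and has no confirmatory alternative; the branch left undefined may well be the one that applies. The condition protects nothing, because a fixed ANCOVA with 67 per group keeps about 5% type I error under the skewness tried.

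The likely cost is an unclear primary result and, if a rank test on change is substituted, roughly 40–50% of the power in relative terms (1 − 37/70 = 47%, 1 − 26/52 = 50%, 1 − 21/35 = 40%), together with a result that no longer estimates the difference in means used to size the trial. Inflation of the error rate is conditional on choosing by result and should not be presented as a consequence of the text itself. All simulated figures depend on assumed count distributions, and the power figures also on an assumed effect and on the doubled 2-week baseline. This should be corrected, but it does not invalidate the design.

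**What to change.** Delete the condition and replace it with one sentence, for example:

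> The primary analysis is ANCOVA of attack frequency over the 4 treatment weeks, adjusted for baseline attack frequency, age, gender, disease duration and study site, whatever the distribution of the outcome. The hierarchical Poisson model is a prespecified sensitivity analysis and does not replace it.

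Baseline attack frequency is already available, since the 10-week diary covers the 2-week screening period (2 + 4 + 4 weeks). Robust standard errors may be added but are optional; ordinary ANCOVA was adequate in the simulations.

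Cost: one sentence, and slightly wider intervals if robust standard errors are used. Sample size, data collection and patient burden are unchanged. The Trial status section reports 12 patients included, so at the time of the article the change could be made before outcome data are examined.

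### The primary ANCOVA names its covariates but omits baseline angina frequency, which the screening diary should already supply: a loss of precision, not a bias

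*Protocol article*

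**What the plan says.** All references are to the protocol article; no separate analysis plan is shown.

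- **Primary outcome:** "the primary outcome is the frequency of angina attacks from baseline to 4 weeks after inclusion". Attacks are counted from a diary kept "throughout the whole 10 weeks observation period".
- **Study design:** "This trial will include a 2-week screening period, a 4-week treatment period, and a 4-week follow-up period". These periods add up to the diary's 10 weeks (2 + 4 + 4), so the diary includes the weeks before randomisation.
- **Inclusion criteria:** patients need "the attack frequency ≥ twice a week in the most recent month". There is a lower limit and no upper one.
- **Data analysis:** for the primary outcome, "if the distribution conforms to the approximately normal distribution, analysis of covariance (ANCOVA) will be used". Centre effects are to be in the model, and then: "Age, gender, duration of the disease, and study site will be included in the model as covariates". Baseline attack frequency appears neither here nor in any other description of the model.
- **Data analysis, secondary outcomes:** "Separate ANCOVA analyses will be performed for secondary outcomes", with no covariates named for them.
- **Sample size:** "assuming α = 0.05 (both sides), 1-β = 0.80". The means, 5.57 and 3.14, are improvements in attack frequency, with σ = 5 and 67 per group. The calculation makes no allowance for covariates.

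**The concern.** The baseline value of an outcome is usually its strongest single predictor. Here the protocol goes as far as choosing three patient-level covariates plus site, and passes over that one. An article may leave model detail to an analysis plan, but this is a stated choice. If an unseen plan adds baseline, it departs from the published list, so the list needs correcting either way.

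Two things are at stake. The first is precision: between-patient variation that baseline could explain stays in the error term. The second is chance imbalance. Entry has a floor of two attacks a week and no ceiling, so starting rates may vary widely, and two groups of 74 can differ at baseline by chance. How much of that difference reaches the treatment estimate depends on what the dependent variable is:

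- If it is the 4-week frequency, the imbalance carries over in proportion to the regression of follow-up on baseline.
- If it is the change, subtraction removes part of it. With equal variances and correlation r, a remainder of (1 − r) of the imbalance is left, in the opposite direction: 50% at r = 0.5 and 20% at r = 0.8.

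The outcome wording does not settle which of the two is meant, although the sample size section points to change. With baseline in the model, the estimated treatment effect is the same for either (apart from the sign convention for improvement), provided both are expressed in the same time unit.

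**Working it through.** **Inputs from the Sample size section:** μ1 = 5.57, μ2 = 3.14, so δ = 2.43; σ = 5; two-sided α = 0.05; power 0.80; 67 per group before dropout.

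**Assumptions, not in the document:** σ = 5 is the SD of the change; baseline and follow-up variances are equal; the baseline/follow-up correlation r takes the values 0.3, 0.5, 0.7 and 0.8.

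**Step 1: the plan's own figure.** n = 2σ²/δ² × (1.960 + 0.842)² = 50/5.905 × 7.849 = 66.46, rounded up to 67. The stated figure reproduces with no baseline adjustment. Power at 67 per group is 80.3% by the normal approximation and 79.7% by the two-sided t-test.

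**Step 2: residual SD with baseline as a covariate.** If the SD at each time is s, then Var(change) = 2s²(1 − r) and the ANCOVA residual variance is s²(1 − r²). Their ratio is (1 − r²)/[2(1 − r)] = (1 + r)/2, so the residual SD is 5 × √[(1 + r)/2].

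**Step 3: power at 67 per group.** The noncentrality is δ/(SD × √(2/67)) = 2.43/(0.1728 × SD). The n for 80% power is 66.46 × variance ratio, rounded up.

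| Model | Variance ratio | SD | Noncentrality | Power (t-test) | n per group for 80% |
|---|---|---|---|---|---|
| Change, no baseline term | 1.00 | 5.00 | 2.81 | 79.7% | 67 |
| Baseline added, r = 0.3 | 0.65 | 4.03 | 3.49 | 93.4% | 44 |
| Baseline added, r = 0.5 | 0.75 | 4.33 | 3.25 | 89.7% | 50 |
| Baseline added, r = 0.7 | 0.85 | 4.61 | 3.05 | 85.7% | 57 |
| Baseline added, r = 0.8 | 0.90 | 4.74 | 2.97 | 83.7% | 60 |

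**Step 4: relaxing equal variances.** If the follow-up SD is k times the baseline SD, the variance ratio becomes k²(1 − r²)/(1 + k² − 2rk).

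| k | r = 0.3 | r = 0.5 | r = 0.7 |
|---|---|---|---|
| 0.7 | 0.417 | 0.465 | 0.490 |
| 1.0 | 0.650 | 0.750 | 0.850 |
| 1.3 | 0.805 | 0.912 | 0.991 |

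The gain can therefore be much larger than in step 3, or almost nothing (k = 1.3 with r = 0.7).

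**Step 5: the other reading of σ.** If 5 is the SD of the follow-up frequency, the residual variance is a fraction 1 − r² of the unadjusted one: 0.91, 0.75 and 0.51 at r = 0.3, 0.5 and 0.7. Power at 67 per group then goes from 80.3% to 83.9%, 90.1% and 97.6% (normal approximation). The direction is the same.

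**The case against.** The strongest reply is that nothing is broken. Randomisation keeps the listed model valid, the trial was sized without baseline adjustment, and on the change reading the planned 80% is met as written. That stands, and it limits the severity.

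It is also true that no baseline/follow-up correlation is given, that σ is not labelled as the SD of change or of a single period, and that the gain depends on how the two variances compare. The omission is certain; its size is not.

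A third reply is that the list may not be exhaustive, or that the word ANCOVA implies a baseline term. The sentence does not say that these are the only covariates. But it names each of them, and baseline is not among them, so this defence is weak.

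Stronger readings that the document does not support:

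- **The trial is badly underpowered.** A reader might take SD 5 as the SD of change, derive a single-period SD of 5/√[2(1 − r)] (6.5 at r = 0.7, 7.9 at r = 0.8), and find 58% or 42% power for an unadjusted 4-week count. That pairs a count outcome with a change-score SD, a mismatch the document nowhere states. If 5 is the SD of the count, unadjusted power is about 80% at any correlation; if it is the SD of change, the sample size section implies a change outcome.
- **Baseline imbalance passes in full into the treatment contrast.** On the change reading, only the remainder described above is left.
- **The secondary analyses are wrong as well.** The article names no covariates for them, and that silence is ordinary condensation, not an error.
- **Every patient will have a complete baseline diary.** The schedule provides for one, but the article itself plans for missing data.

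**Conclusion.** The point holds as a loss of efficiency in the primary analysis. The published list leaves out the baseline value of the outcome although the design collects it. On the change reading with equal variances, adding it would raise power by about 4 to 14 percentage points over correlations of 0.8 down to 0.3, from a base of about 80%. If the follow-up variance is clearly larger than the baseline variance, the gain may be close to nil. In large samples, adjusting for baseline is at no point less precise than leaving it out.

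There is no bias, and the total of 148 is not too small because of this omission. Severity: should-fix. Confidence is high that the term is missing and low on the exact gain.

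**What to change.** Put baseline weekly angina attack frequency, taken from the screening diary, at the head of the covariate list in the Data analysis section, and leave the four existing covariates as they are. Because the article does not define baseline frequency, the same sentence should say that it is the screening-diary count per week. Expressing the outcome per week too puts both on one time scale. It would also help to state whether the dependent variable is the change or the treatment-period frequency; once baseline is in the model, that choice no longer affects the treatment effect.

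The same adjustment is advisable for secondary outcomes measured both at baseline and later. It cannot apply to treatment expectation, which is measured at baseline only and would be adjusted for itself.

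The cost is one sentence and one degree of freedom, with no new data collection and no change to the sample size. It should be made before unblinding so that it cannot look data-driven. The article reports 12 patients included so far, so it can still be pre-specified cleanly.
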